| V2 | 08/16/2016 | - Clarified that this evaluation does not assume that there is an association between PCV13 exposure and Kawasaki disease. - Deleted objective to explore the role of concomitant vaccines. - Included the ICD-10 code based algorithm in addition to ICD-9 code based algorithm for identifying Kawasaki disease. Clarified in the text that we will evaluate the positive predictive values of the ICD-9 and ICD-10 code based algorithms for Kawasaki disease separately and combined together. - Increased the number of Data Partners from 4 to 6. - For the study population, both exposed and unexposed to PCV vaccine, we further explained the number of days continuously enrolled in the Data Partner. - Removed CPT code for PCV7 vaccination and added CPT code for unspecified PCV vaccine exposure code. - For the outcome definition, added the ICD-10 code for acute febrile mucocutaneous lymph node syndrome and explained codes in the inpatient setting will be in any position (primary diagnosis, secondary diagnosis, etc.). - For the outcome definition, further explained what the first code in 365 days in the inpatient setting will include. - Changed the number of days following all doses of PCV13 vaccines from 38 to 42 days in order to identify cases whose symptoms began within the 28 day risk window. Also specified the risk window applies to PCV13 as opposed to PCV. - For the self-controlled analysis, added that diagnoses that occur up to 14 days beyond the end of the control window will be captured. Also explained how cases will be classified. There will be no censoring of person-time within risk windows and control windows. - Clarified that the unadjusted analysis in the self-controlled analysis will use logistic regression. - For the Cohort Poisson Regression Analysis, exposed person-time will include from the time of licensure of PCV13 (February 2010) to the most up-to-date data. - Attempting to include state/zip code as a proxy for race/ethnicity in the model for the Cohort Poisson Regression Analysis has been removed. - For the Cohort Poisson Regression Analysis, the unexposed time period has been clarified. - A secondary cohort analysis has been added with a defined risk interval to further explore findings from a prior study regarding vaccination associated with Kawasaki disease incidence. - State/zip code as a surrogate for race/ethnicity has been removed from the section on potential confounders and effect modifiers. - Deleted Exploring the Role of Concomitant Vaccines section. - ICD-10 code M30.3 for acute febrile mucocutaneous lymph node syndrome has been added to the automated code analysis section. - Deleted the Post-study Combined Analysis section - A reference for a prior study (Abrams et al.) has been added. | Sentinel Operations Center Kawasaki Disease and PCV13 Vaccine Workgroup |

# Introduction

The Post-Licensure Rapid Immunization Safety Monitoring (PRISM) program was established in August 2009 as one of several 2009 H1N1 influenza vaccine safety surveillance efforts launched and supported by the federal government. In September 2010, PRISM was incorporated into what was then Sentinel’s pilot project, Mini-Sentinel, to provide FDA with an active surveillance capability for vaccines to inform regulatory decision-making. The transition to Sentinel occurred in FY2015. To further explore a potential safety signal seen in the Vaccine Adverse Event Reporting System (VAERS),[^1^](#_ENREF_1) this protocol describes an effort to evaluate whether an increased risk of Kawasaki disease is associated with receipt of the 13-valent pneumococcal conjugate vaccine (PCV13). If an association is observed, then its magnitude will be quantified.

# Background

## Public Health Significance and Study Motivation

Pre-licensure trials of both PCV7 (Prevnar; Wyeth) and PCV13 (Prevnar13; Wyeth) vaccines found no increased risk for serious adverse events.[^2^](#_ENREF_2) In a post-licensure safety study unadjusted analysis, however, an increase in Kawasaki disease hospitalizations among PCV7 vaccinated patients was reported when compared to historical controls.[^3^](#_ENREF_3) Further analysis adjusted for sex, race, age at first dose, length of follow-up and season, found no evidence for an association of Kawasaki disease with the PCV7 vaccination.[^3^](#_ENREF_3) Hua et al. explored 29 reports of Kawasaki disease reported for PCV7 vaccination to the Vaccine Adverse Events Reporting System (VAERS) from 1990-2007. The evaluation did not suggest an elevation of the risk of Kawasaki disease following PCV7.[^4^](#_ENREF_4) Post-licensure surveillance of the PCV13 vaccine in the Vaccine Safety Datalink (VSD) compared the cumulative risk of Kawasaki disease within 28 days of vaccination with PCV13 to the historical risk within 28 days of vaccination with PCV7 from 2007 to 2009. A statistical signal for Kawasaki disease after PCV13 was identified at the second group sequential test (of the 12 group sequential tests over a 90-week period that had been planned for each of the 7 health outcomes of interest). Subsequently, the investigators conducted a single end-of-study analysis of Kawasaki disease, in which they obtained medical records to adjudicate each case identified by automated Kawasaki disease diagnoses. Using confirmed cases only, the risk within 0-28 days following vaccination with PCV13 when compared to PCV7 was 2.38 (0.92, 6.38). This result was not found to be statistically significant and was not controlled for race/ethnicity. The study authors noted that the possible association between PCV13 and Kawasaki disease, as suggested by the elevated relative risk estimate, may deserve further investigation.[^5^](#_ENREF_5) A review of the first 18 months of licensure of PCV13 was completed by the FDA under the FDA Amendment Act of 2007 section 915. This review included an analysis of the PCV13 VSD study results as well as an evaluation of the VAERS proportional reporting ratios (PRR) for Kawasaki disease. The review resulted in an FDA internet posting that reported there had been adverse event reports of Kawasaki disease following administration of PCV13. This 915 posting also stated that the FDA intended to initiate a larger study of Kawasaki disease risk following PCV13 vaccination in PRISM.[^1^](#_ENREF_1)

The present protocol describes the study that will be conducted to fulfill the FDA commitment to further explore the possible relationship between PCV13 vaccination and Kawasaki disease. This evaluation does not a priori assume that there is an association between PCV13 exposure and Kawasaki disease.

## PCV13

Infection by *Streptococcus pneumoniae* is identified by the World Health Organization (WHO) as a major cause of pneumonia, bacteremia and meningitis. Although over 90 pneumococcal serotypes have been identified, a small subset of serotypes account for the majority of disease.[^6^](#_ENREF_6) Prior to licensure of the pneumococcal conjugate vaccine, young children were highly susceptible to pneumococcal disease, with an estimated 17,000 cases of invasive disease and 200 resulting deaths occurring annually in children ≤5 years of age in the United States. An additional 5 million cases per year of acute otitis media were believed to result from pneumococcal disease in children ≤5 years of age.[^7^](#_ENREF_7)

In 2000, FDA licensed the first pneumococcal conjugate vaccine, 7-valent pneumococcal vaccine (PCV7) (Prevnar; Wyeth), for use in infants and young children. PCV7 protected against strains of *Streptococcus pneumoniae* that most commonly caused illness among children in the U.S. Subsequently, inclusion of PCV7 in the recommended children immunization program resulted in decreased rates of invasive pneumococcal disease.[^8^](#_ENREF_8) The CDC reported that rates of PCV7-type invasive pneumococcal disease in children under 5 years of age dropped from 80 cases per 100,000 to less than 1 case per 100,000 following the implementation of the PCV7 vaccine.[^9^](#_ENREF_9) FDA licensed a second vaccine, PCV13 on February 24^th^, 2010 to protect against 6 additional serotypes that accounted for much of the invasive pneumococcal disease in young children not covered by the PCV7 vaccine.[^10^](#_ENREF_10) The Advisory Committee on Immunization Practices (ACIP) recommended PCV13 for use as a 4-dose vaccination series, administered at 2, 4, 6 and 12-15 months of age, similar to the PCV7 vaccine recommendations. Full implementation of the transition from PCV7 to PCV13 came into effect in March 2010 with supplies of PCV13 available to the public sector that month as shown in Figure 1.[^11^](#_ENREF_11) By July 2010, Pfizer reported that >90% of its private shipments of pneumococcal conjugate vaccines were for PCV13.[^11^](#_ENREF_11) Children previously vaccinated with PCV7 finished their remaining vaccinations with PCV13. A dose of PCV13 was recommended by ACIP for children 14-59 months of age who had completed the 4-dose vaccination series with PCV7, and children with specified underlying medical conditions receive a 5^th^ dose until 71 months of age.[^10^](#_ENREF_10)

[figure not shown]

Figure 1. “Pneumococcal conjugate vaccine doses administered to children aged 0 through 59 months, by vaccine type and week --- Immunization Information System sentinel sites, United States, March 7--August 21, 2010.” [^11^](#_ENREF_11)

## Kawasaki Disease

Kawasaki disease is an acute, self-limited vasculitis and is the leading cause of acquired heart disease in children in the United States. Kawasaki disease primarily affects infants and young children, as shown in Figure 2 and Figure 3. The etiology of Kawasaki disease is unknown, although theories include an infectious cause or immunologic response triggered by an infectious agent.[^12^](#_ENREF_12)^,^[^13^](#_ENREF_13) No disease-specific laboratory test is available. Hence, the diagnosis of Kawasaki disease is based on a clinical case definition as described by the American Heart Association, which specifies that patients have fever lasting for ≥5 days (or fever until the date of administration of intravenous immunoglobulin) and at least 4 of the following 5 primary clinical features.[^13^](#_ENREF_13)

1. Changes in the extremities (erythema of palms or soles; edema of hands or feet; periungual peeling of fingers or toes)
2. Polymorphous exanthem rash
3. Bilateral conjunctival injection without exudates
4. Changes in lips and oral cavity (inflamed lips or throat, strawberry tongue, or dry/cracking lips)
5. Cervical lymphadenopathy (at least 1 lymph node ≥ 1.5 cm in diameter)

“Incomplete” or “atypical” Kawasaki disease can also be diagnosed in patients presenting with fever for ≥5 days and <4 of the clinical features, if coronary artery disease is diagnosed using echocardiography or coronary angiography.[^13^](#_ENREF_13) The diagnosis of incomplete Kawasaki disease is more common in infants <6 months of age, and these patients are more likely to develop coronary artery abnormalities as compared with infants between 6 and 12 months of age.[^13-15^](#_ENREF_13) In general, physicians are encouraged to consider a diagnosis of Kawasaki disease in febrile patients with fewer clinical features of Kawasaki disease in the absence of cardiac complications for prompt treatment to reduce the risk of coronary artery aneurysms.[^16^](#_ENREF_16) If left untreated, approximately 25% of patients develop coronary artery aneurysms which may lead to additional cardiac complications including myocardial infarction, sudden death or ischemic heart disease.[^13^](#_ENREF_13)^,^[^17^](#_ENREF_17)^,^[^18^](#_ENREF_18) Intravenous immunoglobulin administration has been identified as a successful treatment in reducing cardiac complications in Kawasaki disease patients if promptly administered within 10 days of illness onset. Aspirin is also used in the treatment of Kawasaki disease for the anti-inflammatory and anti-platelet effects.

Numerous factors have been shown to affect the incidence of Kawasaki disease in the United States. The illness presents most commonly in Americans of Asian and Pacific Island descent, with an incidence of 32.5/100,000 in children <5 years of age compared to 9.1/100,000 for non-Hispanic whites of the same age group.[^13^](#_ENREF_13)^,^[^19^](#_ENREF_19) In addition, Kawasaki disease is age-dependent, with 80% of cases occurring before age 5 years, and a peak incidence at 13-24 months of age.[^20^](#_ENREF_20) Many studies have reported increased incidence of Kawasaki disease in males, with male to female ratios ranging from 1.5-1.7 : 1.[^4^](#_ENREF_4)^,^[^7^](#_ENREF_7)^,^[^19^](#_ENREF_19)^,^[^21^](#_ENREF_21)^,^[^22^](#_ENREF_22) Seasonality is also believed to have some impact on incidence.[^19^](#_ENREF_19)

[figure not shown]

Figure 2. “Number of cases in the National Inpatient Sample (NIS) data presented by patients’ age. The number of cases peaks at patients 1 to 2 years of age, followed by patients <1 year and 2 to 3 years of age, and then the number continues to decrease towards older age.”[^23^](#_ENREF_23)

[figure not shown]
Figure 3. “Kawasaki syndrome associated hospitalizations and cumulative percent by … age in months for children <5 years, United States, 2006.”[^24^](#_ENREF_24)

# Objectives

The objectives of this study are:

1. To determine the existence and magnitude of any increased risk of Kawasaki disease in the 28 days following PCV13 vaccination.
2. To determine through medical chart review the positive predictive value of an ICD-9 and ICD-10 code based algorithm for identifying Kawasaki disease.

# Methods

## Study Population and Data Sources

Six Data Partners will participate in this evaluation, and all will have data available from 2008 until the most recent data refresh. The study population will include infants and children from birth until 23.99 months of age who were members of the participating Data Partners during 2008 to 2015 and who meet the other enrollment criteria. When the data analysis programs are run, we will use the most up-to-date information from each Data Partner.

Infants and children meeting the following criteria will be included in the evaluation:

- Exposed to at least 1 dose of PCV vaccine and continuously enrolled in the Data Partner from birth through at least 84 days (risk and control intervals (56 days) plus 28 days to account for delays in symptom onset and Kawasaki disease diagnosis coding) after their first dose of PCV vaccine.
- Unexposed to PCV vaccine and continuously enrolled in the Data Partner from birth through at least 144 days of age (60 days, the time that many infants would receive dose 1, plus 84 days), with at least one documented healthcare visit in any setting between 14 and 150 days.

Gaps of up to 45 days between birth and enrollment will be allowed. For both exposed and unexposed categories of subjects, continuously enrolled person-time through a maximum age of 23.99 months will be included in the analyses, with the following proviso:

- If an infant in the exposed category has incomplete person-time during *0-84 days after Dose 2* of PCV vaccine, his/her person-time on and after the day of that vaccination will be excluded;
- If a child in the exposed category has incomplete person-time during *0-98 days after Dose 3 or 4* of PCV vaccine, his/her person-time on and after the day of that vaccination will be excluded.

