## Outcome Definition

Cases of Kawasaki disease will be identified by the ICD-9 code 446.1 and ICD-10 code M30.3 (acute febrile mucocutaneous lymph node syndrome) in the inpatient setting in any position (primary diagnosis, secondary diagnosis, etc.). We assume that a confirmed or suspected case of Kawasaki disease would be admitted to a hospital to initiate treatment or undergo further clinical evaluation. Only the first code in 365 days in the inpatient setting for patients at least 365 days of age or first ever for those under 365 days of age will be considered in order to exclude follow-up visits for Kawasaki disease.

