### Overview of hypothesis-testing analyses

A challenge in studying PCV13 and Kawasaki disease will be the confounding effect of age, as both vaccination and the risk of Kawasaki disease are age-dependent. To confront this challenge, we will use both a *self-controlled risk interval (SCRI)*[*^26^*](#_ENREF_26)*^,^*[*^27^*](#_ENREF_27) and a *cohort* design. A major advantage of the former, which we are pre-specifying as the primary method, is that it inherently controls for all fixed (non-time-varying) potential confounders such as gender, race/ethnicity, and chronic predisposing conditions, by virtue of each subject serving as his/her own control. Another advantage of the SCRI design is that it uses only exposed cases, thus minimizing potential misclassification bias due to incomplete data on vaccine exposure. A possible disadvantage is that adjustment for time-varying confounders such as age must be made explicitly, and estimation of the age effect may introduce error. The cohort design is likely to have higher statistical power than the self-controlled design, due to the relatively large amount of historical and concurrent unexposed data involved in the generation of expected counts. However, its ability to control for time-invariant confounding is not as good as that of the self-controlled approach. If there are differences among racial/ethnic groups in vaccine coverage and timing, an important potential confounder in the cohort design will be race/ethnicity. The point estimates are also subject to bias from misclassification of exposure if some vaccinations are not recorded in the claims data and not captured during the chart review process.

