In a secondary analysis, we will adjust for age with conditional Poisson regression. The outcome will be the occurrence of Kawasaki disease. We will compare the risk of Kawasaki disease during the 28-day risk interval after PCV13 to the risk of Kawasaki disease during the 28-day comparison interval, adjusting for the four-week age difference between these two intervals. The risk of Kawasaki disease by week of age will be modeled as a continuous function using either polynomials or splines. The selection of the best-fitting polynomial or splines to describe the risk-by-age relationship will be done without including the risk interval in the model, to ensure integrity of the results. This method will estimate the incidence curve by age from PRISM Kawasaki disease rates in all eligible exposed or unexposed time. In the Poisson regression, the conditioning will be done on individuals, ensuring a self-controlled analysis. This means that individuals without the outcome in either the risk or the control interval are only used to estimate the incidence curve by age, while individuals with the outcome in either the risk or control interval are used to estimate both the incidence curve and the risk of Kawasaki disease associated with the vaccine.

Because the sample size to be used for the age adjustment is larger in the Holman et al. study than it is expected to be in our study population, the first method is preferable, in our view. Note that, if the incidence estimate is off by the same magnitude at all ages, for example, 10% higher than actual at all ages, it is inconsequential for a self-controlled analysis.

Study design and analysis methods are shown in Table 1.

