### Cohort Poisson Regression Analysis

The second design that we will use is a cohort design with unconditional Poisson regression, including the exposed person-time from the time of licensure of PCV13 (February 2010) to the most up-to-date data, and unexposed person-time for the entire cohort from the year 2008 to the most up-to-date data. The following covariates will be included in versions of the Poisson regression model before settling on the most parsimonious and explanatory model: vaccination risk window (yes/no), age in weeks modeled as a continuous variable, sex, and calendar year as a continuous variable, and Data Partner. It is not feasible to include race/ethnicity as a covariate in this analysis as that information is not widely available in the Sentinel data. Exposed person-time will be the 1-28 days after PCV13 vaccination, while unexposed time will be the time outside of the 7 days before through the 42 days after vaccination with either PCV13 or PCV7. (We exclude the 7 days prior to vaccination from unexposed time in order to control for the healthy vaccinee effect and similar effects that could result from dependency of vaccination on one’s health condition in the week prior.) We will include unexposed person-time from children who are not vaccinated with PCV7 or PCV13 but have at least one documented healthcare visit. A polynomial risk function will be used to refine estimates of background rates by week of age during the first 1.5 years of life. We will systematically try at least linear, quadratic, cubic, fourth-order, and fifth-order functions, without exposure in the model (to blind ourselves to the effect of vaccination), and select the function to include in the final model based on the log-likelihood ratio, p-value, Akaike information criterion (AIC), and biologic plausibility. If we cannot find a well-fitting polynomial function, we will try splines instead.

Dose PCV13 Kawasaki disease

unexposed exposed unexposed

Figure 5. Cohort design to evaluate the incidence rate ratios comparing rates in the exposed and unexposed intervals

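### The visit criterion for never-vaccinated children can be met by the Kawasaki admission itself, so their entry into the cohort analysis can depend on the outcome at 14-150 days of age

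*Protocol*

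**What the plan says.** Protocol, Study Population and Data Sources, sets two conditions for children not exposed to PCV. They must be "continuously enrolled in the Data Partner from birth through at least 144 days of age", and they must be included "with at least one documented healthcare visit in any setting between 14 and 150 days".

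The Cohort Poisson Regression Analysis section repeats the visit condition without ages: "We will include unexposed person-time from children who are not vaccinated with PCV7 or PCV13 but have at least one documented healthcare visit".

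Under Outcome Definition, a case is a child with an inpatient Kawasaki code, and the section assumes that confirmed or suspected cases are admitted. No section excludes that admission from counting as the visit, or requires the visit to come before the illness.

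Unexposed time is not drawn from never-vaccinated children alone. In the cohort analysis, "unexposed time will be the time outside of the 7 days before through the 42 days after vaccination with either PCV13 or PCV7", so vaccinated children contribute as well.

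**The concern.** An inpatient stay is a visit in any setting. Every never-vaccinated child admitted with Kawasaki disease at 14-150 days therefore meets the visit condition automatically. A never-vaccinated child who stays well and has no contact in that window fails it and is removed with all follow-up. In that age band, cases and person-time in the never-vaccinated group are thus selected by different rules.

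Taken alone, this raises the unexposed rate and lowers the cohort rate ratio, which is the direction that could hide a risk. The ages affected matter: on the recommended schedule the dose 1 and dose 2 risk windows both lie inside 14-150 days. The Cohort section also promises a table of unexposed cases and person-days by week of age, where the affected cells would appear.

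**Working it through.** **The plan's own figures.** The protocol gives no figure for the visit criterion or for the cohort analysis. Its power table (Table 2) concerns the self-controlled design and supplies two inputs: 3,388,104 PCV13 doses and 8.7 cases per 100,000 person-years. Expected control-window cases are 3,388,104 × 28/365.25 × 0.000087 = 22.6. At a relative risk of 1.9 the total is 22.6 × 2.9 = 65.5 cases, and normal approximations give 79.5-80.7% one-sided power against the stated 80.0%. The inputs are therefore read correctly. That power does not change with this point.

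**Person-time layout.** The PCV13 section says doses are "administered at 2, 4, 6 and 12-15 months of age". I place them at days 60, 120, 180 and 400 and follow children to day 730.
- Each dose removes days -7 to +42, which is 50 days. A fully vaccinated child has 730 - 4 × 50 = 530 unexposed days.
- Days 14-150 are 137 days. The first two exclusions cover days 53-102 and 113-162, leaving days 14-52 (39) and 103-112 (10): 49 unexposed days.
- The dose 1 and 2 risk windows are days 61-88 and 121-148. An on-schedule child has no unexposed time in either. Same-age comparison time comes from never-vaccinated and off-schedule children, with the fitted age curve borrowing from neighbouring ages.

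**Assumptions not in the protocol.** u = share never vaccinated, 2-10%. f = share of those with no other visit at 14-150 days, 5-50%. The rate is flat at 8.7 per 100,000 person-years. There are 3 to 4 doses per vaccinated child.

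**Formulas.**
- Vaccinated children K = 3,388,104 / doses per child; never-vaccinated children = K × u/(1-u).
- Extra cases admitted = never-vaccinated children × f × 137/365.25 × 0.000087.
- Pooled inflation = 137uf / [530(1-u) + 730u(1-f)].
- Inflation at 14-150 days = 137uf / [49(1-u) + 137u(1-f)].
- Inflation among never-vaccinated children at 14-150 days = f/(1-f).

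**Worked case, u = 5%, f = 20%, 4 doses.** K = 847,026, with 44,580 never vaccinated. Extra cases = 44,580 × 0.2 × 137/365.25 × 0.000087 = 0.29, against about 113 expected unexposed cases. Pooled inflation: 1.37/(503.5 + 29.2) = 0.26%. At 14-150 days: 1.37/(46.55 + 5.48) = 2.6%.

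| u | f | Extra cases (4 / 3 doses) | Pooled inflation | Inflation, 14-150 days | Never-vaccinated only, 14-150 days |
|---|---|---|---|---|---|
| 2% | 5% | 0.03 / 0.04 | 0.03% | 0.3% | 5% |
| 5% | 20% | 0.29 / 0.39 | 0.26% | 2.6% | 25% |
| 10% | 50% | 1.54 / 2.05 | 1.33% | 13.4% | 100% |

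Across the whole grid, expected unexposed cases are about 108-163. The pooled inflation multiplies a crude rate ratio by 1/1.0133 = 0.987 at worst. The age-adjusted ratio need not match either inflation column, because it depends on how far the fitted curve borrows across ages.

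The percentages do not depend on the dose total. The case counts do, and the total comes from four Data Partners while six will take part. The Kawasaki Disease section puts peak incidence at 13-24 months; if the rate is lower in early infancy, the flat rate overstates the pooled percentage.

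**The case against.** The strongest reply is that the effect is too small to matter. Most unexposed time comes from vaccinated children, only admissions at 14-150 days in children with no other visit count, and the primary analysis is out of reach: "Another advantage of the SCRI design is that it uses only exposed cases". All of this stands. The only self-controlled analysis that could be touched, and slightly, is the secondary one, whose age adjustment draws on all eligible time: "This method will estimate the incidence curve by age from PRISM Kawasaki disease rates in all eligible exposed or unexposed time". What the reply does not answer is that the effect is concentrated at the dose 1 and 2 ages, where same-age unexposed time is scarce.

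A second reply concerns direction. Under Medical Chart Review, immunization records are sought for Kawasaki cases with no PCV history, but not for the person-time of other apparently unvaccinated children. Correcting cases alone takes cases out of the never-vaccinated group and leaves its denominator, which pushes the rate ratio up. This stands: the net cohort bias cannot be signed from the document.

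Three stronger readings are tempting and are not supported:
- **That admission at any age to 23.99 months confers eligibility.** The Cohort section's wording, read alone, allows this. With 5-10% never vaccinated and 10-40% of them without another visit (assumed), inflation would be 540/536.35 to 550/520.8, or 0.7-5.6%. But Study Population and Data Sources sets inclusion for the whole evaluation, and the Cohort section does not say it replaces it. Under the 14-150 day rule the same inputs give 0.685/536.35 = 0.13% to 5.48/520.8 = 1.05%. Without an age limit, the share lacking any other visit would also be smaller.
- **That the cohort analysis will look falsely protective.** A pooled shift of about 1%, with an opposing error of unknown size, does not establish that.
- **That 144 and 150 days contradict each other.** Enrolment is a minimum, so a visit window ending six days later is workable.

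**Conclusion.** The point holds in a limited form. As written, a never-vaccinated child's eligibility can depend on having the outcome, through admissions at 14-150 days in children with no other visit in that window. The mechanism raises the unexposed rate by about 0.03-1.3% pooled (0 to 2 cases) and by about 0.3-13% within 14-150 days. It lowers the cohort rate ratio to a matching degree before any offsetting error. These sizes rest on the assumed shares u and f, a flat rate and on-schedule dosing. The conclusion that eligibility is outcome-dependent rests only on the protocol's text. The primary result is not in question, and no net direction for the cohort result can be claimed. The correction is worth making because the rule is already fixed in the protocol, is stated in two ways, and is cheap to repair.

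**What to change.** 1. State the visit criterion once, with the 14-150 day window, and use it identically in Study Population and Data Sources and in Cohort Poisson Regression Analysis.
2. Do not count an encounter carrying a Kawasaki disease code as the qualifying visit.
3. Start a never-vaccinated child's person-time at the qualifying visit, so that cases and event-free time before it are left out alike. Merely requiring the visit to precede any Kawasaki encounter is not enough. It would drop a child with Kawasaki disease at day 40 and a routine visit at day 60, while keeping the pre-visit time of well children, which biases the other way.

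If cohort cases are dated by symptom onset, as the Risk Window section does when assigning windows, a visit prompted by the presenting fever would fall after onset and could not bring the case in. The cohort section should state that dating.

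At minimum, keep the present rule and report a sensitivity analysis that excludes cases qualifying only through the Kawasaki admission.

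The cost is a few words and a small change to the cohort program. A few unexposed cases and some early never-vaccinated person-time are lost, at ages where such time is already thin.
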